## Abstract

**Background::**

Acute myocardial infarction is a very common disease in the emergency room. Emergency percutaneous coronary intervention (PCI) is the first choice to open infarct-related artery in time to regain the active blood flow of myocardial tissue. Clinical nursing pathway (CNP), namely clinical project, is an original nursing mode with good quality, outstanding efficiency, and low treatment spending, so it has attracted more and more attention. However, few studies have reported the implementation of a CNP in PCIs. The purpose of the protocol is to assess the impact of CNP on the clinical efficacy of transradial emergency PCI.

**Methods::**

This is a randomized controlled, single center trial which will be implemented from January 2021 to June 2021. Hundred samples diagnosed with acute myocardial infarction will be included in this study. It was authorized via the Ethics Committee of Changshan County People's Hospital (CCPH002348). Patients are assigned to the following groups: control group, given normal routine care; CNP group, treated with CNP plan. The time from door to balloon, hospitalization expenses, length of stay, postoperative complications, patients’ satisfaction with treatment are compared and analyzed. All data are collected and analyzed by Social Sciences software version 21.0 (SPSS, Inc., Chicago, IL) program.

**Results::**

Differences of clinical outcomes between groups (Table 1).

**Conclusion::**

This original evidence-based nursing model can be used as the foundation for further research.

**Trial registration number::**

researchregistry6030

## Introduction

1

Cardiovascular disease (CVD) is one of the main causes of human death.^[1]^ According to the 2015 Global Burden of Disease Research, there were 427.7 million CVD cases and 17.92 million CVD-related deaths in 2015. It has been predicted that the number of deaths due to heart disease will reach 23.3 million by 2030.^[2]^ Approximately 50% of mortality related to CVD is caused by coronary atherosclerotic heart disease.^[3]^ Patients with severe or instable coronary heart disease need percutaneous coronary intervention (PCI).^[4,5]^ Current treatment options suggest that patients with acute ST segment elevation myocardial infarction should be dealt with PCI.^[6,7]^ With the increase of life expectancy, there will be more and more elderly patients with coronary heart disease.

The risks related to PCIs differ greatly, and special care is needed in independent and collaborative settings. Risk elements such as age, anticoagulation therapy, repeated PCI, gender, and arterial access management have a great influence on consequences.^[8–10]^ Medical management and secondary prevention strategies for PCI are procurable from international organizations. The role of nurses and the influence of nursing interventions on health consequences are rarely described and analyzed in these guidelines. At present, with the rapid progress of medical technology, the nursing mode must be updated accordingly. Clinical nursing pathway (CNP), namely clinical project, is an original nursing mode with good quality, outstanding efficiency, and low treatment spending, so it has attracted more and more attention.^[11,12]^ However, few studies have reported the implementation of a CNP in PCIs. The purpose of the protocol is to assess the impact of CNP on the clinical efficacy of transradial emergency PCI.

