### Subjects

2.2

Hundred patients with diagnosed acute myocardial infarction (AMI) will be included in this experiment. In the random envelope, a random number is assigned to whole patients through the random-number table, and the distribution result is invisible. Patients are assigned randomly to the following groups:

(1)control group, accepting normal nursing plan, containing 50 patients;(2)CNP group, treated with CNP plan.

Patient inclusion criteria contains:

(1)acute ST segment elevation myocardial infarction;(2)emergency transradial PCI therapy is necessary.

Patient exclusive criteria contains:

(1)Damage to organs such as kidney, lung, and so on;(2)Malignant tumor;(3)a history of coagulopathy, a history of the history of renal and hepatic dysfunction.

Ensure that informed consent forms signed by all participants have been collected.

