### Statistical analysis

2.5

All data are collected and analyzed by Social Sciences software version 21.0 (SPSS, Inc., Chicago, IL) program. The categorical variables are expressed as percentage of patients and analyzed by the Fisher exact test or Pearson Chi-square test. Continuous variables are showed as mean (standard deviation) and analyzed by paired *t* tests or independent *t* tests. The *P*-value of significance level is set to be less than .05.

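### The stated tests are valid but unadjusted; adjusting the continuous outcomes for age, gender and prior PCI would be a cheap, modest improvement

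*Protocol article*

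**What the plan says.** - **Prognostic factors.** The Introduction, writing about the risks of PCI, states: "Risk elements such as age, anticoagulation therapy, repeated PCI, gender, and arterial access management have a great influence on consequences".
- **Analysis.** Section 2.5 (Statistical analysis) assigns tests by type of variable. For continuous outcomes: "Continuous variables are showed as mean (standard deviation) and analyzed by paired *t* tests or independent *t* tests". For categorical outcomes: "The categorical variables are expressed as percentage of patients and analyzed by the Fisher exact test or Pearson Chi-square test". The threshold is given as "The *P*-value of significance level is set to be less than .05". No regression or other covariate model is named.
- **Size and allocation.** Section 2.2 (Subjects) says "Hundred patients with diagnosed acute myocardial infarction (AMI) will be included in this experiment" and describes one arm as "control group, accepting normal nursing plan, containing 50 patients". The size of the clinical nursing pathway arm is not stated; 100 − 50 = 50 is inferred. On allocation it says "a random number is assigned to whole patients through the random-number table, and the distribution result is invisible". No stratification or minimisation is described.
- **Outcomes.** Section 2.4 lists door-to-balloon time, expenses, length of stay, complications and satisfaction.

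**The concern.** The factors that the article calls highly influential enter neither the allocation as described nor the analysis as stated. Two things follow in a trial of 100.

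First, outcome variation that baseline factors could explain stays in the error term of the t test. Intervals for the continuous outcomes may then be wider than they need to be.

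Second, simple randomisation of 100 patients often leaves visible differences between arms in individual factors. A crude test cannot correct for them. If covariates are picked only after such a difference has been seen, the adjusted result is open to the charge of selection, so the choice has to be made beforehand.

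This is not just a matter of detail left to another document. Section 2.5 does choose a method, and the point concerns that choice.

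**Working it through.** The article states no power, effect size, SD or event rate, so it has no figure to reproduce. What follows is illustrative.

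**Inputs**
- From the article: 100 patients, 50 in the control arm, significance level 0.05.
- Inferred: 50 in the pathway arm.
- Assumed: two-sided test; true difference d = 0.5 SD; R² from 0 to 0.25; a binary factor with prevalence 10% to 50%.

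**1. Power of the unadjusted t test**

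SE of the difference = √(2/50) = 0.20 SD. Noncentrality = 0.5/0.20 = 2.50 on 98 df. Power = 69.7%.

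**2. Power with three covariates**

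The residual SD becomes √(1 − R²). Estimating three covariates inflates the variance by about 1 + 3/(100 − 3 − 3) = 1 + 3/94 = 1.032, and leaves 95 df.

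Noncentrality = 2.50 / √[(1 − R²) × 1.032]

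| R² | Noncentrality | Power | Change from 69.7% |
|---|---|---|---|
| 0 | 2.461 | 68.3% | −1.4 |
| 0.02 | 2.486 | 69.2% | −0.5 |
| 0.03 | 2.499 | 69.6% | −0.1 |
| 0.05 | 2.525 | 70.5% | +0.8 |
| 0.10 | 2.594 | 72.8% | +3.1 |
| 0.25 | 2.842 | 80.3% | +10.6 |

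Break-even is near R² = 3%. Without the charge for three covariates, power would be 74.2% at R² = 0.10 and 81.6% at 0.25, which overstates the gain by a little over 1 point.

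**3. How often arms differ by chance**

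For a binary factor, the number of carriers in one arm is hypergeometric (100 patients, 50 per arm).

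| Prevalence | P(difference ≥ 12 points) | P(difference ≥ 16 points) |
|---|---|---|
| 10% | 9.2% | 1.6% |
| 20% | 21.1% | 7.8% |
| 30% | 27.5% | 12.6% |
| 50% | 31.7% | 16.1% |

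For a continuous factor such as age, the standardised difference has SD 0.20. It exceeds 0.2 SD in about 32% of randomisations and 0.4 SD in about 4.6%.

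**4. What an imbalance does to the comparison**

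A binary factor with prevalence 0.30 that explains 10% of the variance has an effect of √(0.10/(0.30 × 0.70)) = 0.69 SD.
- 12-point imbalance: 0.12 × 0.69 = 0.08 SD, or 0.4 standard errors.
- 16-point imbalance: 0.16 × 0.69 = 0.11 SD, or about 0.55 standard errors.

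**5. Type I error, by simulation**

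There were 20,000 trials for each R², with one continuous covariate and no treatment effect. Over all randomisations the t test rejected in 4.8% to 5.1%. Among trials with an imbalance of at least 0.4 SD (about 4% to 5% of them), it rejected in about 12% at R² = 0.10, 16% at 0.20 and 23% at 0.30. Analysis of covariance rejected in about 5% to 6% of the same trials.

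**The case against.** **The tests are valid.** A reader might infer that ignoring prognostic factors biases the result or invalidates the P-value. It does not. Over randomisations the t test keeps its level, and its standard error already allows for chance imbalance. This objection stands: what is lost is efficiency, and protection in the particular trial that turns out unbalanced.

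**The article does not contradict itself.** The Introduction speaks of the consequences of PCI in general. It does not say that age, gender or repeated PCI predict door-to-balloon time, expenses or length of stay, and it gives no strength of association. The outcome nearest to that sentence, complications, is the one least suited to adjustment. This also stands. R² for the three continuous outcomes is unknown and could be near zero.

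**Adjustment is not free.** Below an R² of about 3% it costs a little power. It also requires baseline data, and the article describes no baseline data collection. In addition, repeated PCI is undefined and could mean a second procedure after randomisation, which would be an unsuitable covariate. These points stand and shape the fix.

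**A fuller document may adjust or stratify.** That is possible, since the article excludes neither. But the published text does name its tests, so a suggestion to change them is fair.

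**Typical imbalances are small.** The shifts in step 4 are about half a standard error. So a chance imbalance would usually nudge the comparison and would not by itself create or hide a difference. The serious case is the roughly 1 in 20 randomisations with a large imbalance in a given factor.

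**Conclusion.** The point stands as a cheap, modest improvement to a stated method. Section 2.5 relies only on unadjusted two-group tests, while the Introduction names age, gender and repeated PCI as influential and no stratification is described. Under the assumptions above, adjustment moves power from 69.7% to between 68.3% (R² = 0) and 80.3% (R² = 0.25). It also keeps type I error near 5% when a prognostic factor is badly unbalanced. These figures rest on an assumed effect, 1:1 allocation, a two-sided test and an R² that the article does not supply.

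Three stronger readings are not supported: that the crude analysis is wrong, that the extra precision comes at no cost, and that every interval would narrow. Complications may have to stay unadjusted, and nothing is known about how far these factors predict satisfaction.

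**What to change.** In section 2.5, before any outcome data are seen:
- Make the main analysis of door-to-balloon time, length of stay and expenses a linear regression on arm, age, gender and history of PCI before the index admission.
- State one scale for each outcome (original or log) and how each covariate is coded.
- Report the adjusted difference with its 95% CI, and show the crude comparison beside it.
- Use only factors known before randomisation. Access route is transradial for everyone by eligibility, and anticoagulation may be part of care after allocation, so neither is a clear candidate.
- Leave complications on the unadjusted test if events are few. A logistic model with several covariates would then be unstable, and it would estimate a conditional odds ratio.

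**Cost:** a few lines of text, three baseline items recorded for every patient, and about 1 point of power if the covariates explain nothing.

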## Materials and methods

2

### Study design

2.1

This is a randomized controlled, single-center trial which will be implemented from January 2021 to June 2021. This trial is conducted according to the SPIRIT Checklist of randomized researches. It was allowed by the Ethics Committee of Changshan County People's Hospital (CCPH002348), and it has been registered in the research registry (researchregistry6030).

### Subjects

2.2

Hundred patients with diagnosed acute myocardial infarction (AMI) will be included in this experiment. In the random envelope, a random number is assigned to whole patients through the random-number table, and the distribution result is invisible. Patients are assigned randomly to the following groups:

(1)control group, accepting normal nursing plan, containing 50 patients;(2)CNP group, treated with CNP plan.

Patient inclusion criteria contains:

(1)acute ST segment elevation myocardial infarction;(2)emergency transradial PCI therapy is necessary.

Patient exclusive criteria contains:

(1)Damage to organs such as kidney, lung, and so on;(2)Malignant tumor;(3)a history of coagulopathy, a history of the history of renal and hepatic dysfunction.

Ensure that informed consent forms signed by all participants have been collected.

### Nursing protocol

2.3

The control group is given normal nursing before and after hospitalization. In order to estimate the development of the patient's condition, emergency electrocardiogram examination is performed during hospitalization. To guard against complications, including multiple procedures, such as preoperative skin preparation, constant monitoring of oxygen, vital signs, postoperative injury care, and so on. Under the guidance of doctors, nurses give patients medication and preoperative preparation. CNP group adopted clinical nursing method. The patients is dealt with rapid diagnosis, then there is a more precise examination, equipment of vital signs support and emergency drugs, and quickly transferred to the correlative experts. At the date of hospitalized, the nursing group formulates the corresponding nursing plan according to the current situation of the patients, referring to the domestic and foreign standards, and modified the nursing content on the basis of the matters met in the actual operation. The patients are instructed to complete medication and nursing plan. The nursing group assesses the patient's general condition and uses emergency equipment and appropriate drugs to prevent adverse events. When the patient is discharged from the hospital, he will receive a pamphlet for AMI, introducing healthy lifestyle, drug treatment, and arranging follow-up.

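### CNP starts with rapid diagnosis and the door-to-balloon clock starts at arrival, but only patients already diagnosed are randomised, so part of both precedes allocation

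*Protocol article*

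**What the plan says.** **Who is randomised (2.2 Subjects).** "Hundred patients with diagnosed acute myocardial infarction (AMI) will be included in this experiment". The inclusion criteria read "acute ST segment elevation myocardial infarction;(2)emergency transradial PCI therapy is necessary". Signed consent is required of every participant ("Ensure that informed consent forms signed by all participants have been collected"), and allocation is by envelope: "In the random envelope, a random number is assigned to whole patients through the random-number table". The section does not say when the envelope is opened relative to arrival, diagnosis or consent.

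**What the arms receive (2.3 Nursing protocol).** The account of CNP begins "The patients is dealt with rapid diagnosis, then there is a more precise examination". It goes on to vital-signs support and emergency drugs, and then the patient is "quickly transferred to the correlative experts". A nursing plan made on the day of admission and discharge education come later. Of the other arm it says "The control group is given normal nursing before and after hospitalization", and it lists an emergency electrocardiogram during the hospital stay.

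**What is compared (2.4 Outcomes, 2.5 Statistical analysis, Discussion).** Door-to-balloon time is the first of five outcomes. Continuous outcomes are analysed by t tests, with no covariate named. The Discussion expects CNP to shorten this time markedly but gives no size.

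**The concern.** A patient who enters the trial as already diagnosed cannot then receive a first diagnosis whose speed depends on the randomised arm. Yet diagnosis is the opening component of CNP, and the outcome it would most directly affect is timed from the door.

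Two things are at stake. The first is interpretation. If door-to-balloon time is shorter under CNP, readers will naturally credit the whole pathway, including faster diagnosis, although that step was not randomised. The second is precision. The stretch from door to randomisation cannot be changed by allocation, but it remains inside the outcome and contributes patient-to-patient variation that an unadjusted t test treats as noise.

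**Working it through.** **Order of events.** The article gives no time point for allocation, so the order has to be inferred from its own criteria.

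1. Door: the outcome clock starts.
2. ST-elevation infarction is diagnosed and emergency transradial PCI is judged necessary. Both are inclusion criteria in 2.2.
3. Consent is signed and the envelope is opened.
4. Assigned care is given.
5. Balloon: the outcome clock stops.

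Steps 1 to 3 precede any difference between arms. The first diagnosis falls there. Transfer to specialists, the nursing plan and the discharge steps can all fall in step 4, so only part of the intervention is affected.

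**Effect on the outcome.** Write D = A + B, where D is door-to-balloon time, A is door-to-randomisation time and B is randomisation-to-balloon time. If both arms receive the same care until the envelope is opened, A has the same distribution in each arm. The expected difference in D is then the expected difference in B. There is no bias, but the variance of A is carried into the comparison.

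**Illustration of size.** The article gives no effect size, SD, power or sample-size derivation, so there is no stated figure to reproduce.

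Inputs from the article:
- n = 50 per arm: 100 patients in all, 50 stated for control, 100 - 50 = 50 for CNP.
- alpha = .05. Two-sided testing is assumed, since sidedness is not stated.

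Inputs assumed:
- Standardised effect d = 0.5, with 0.8 as a larger alternative.
- Share f of the within-arm variance of D explained by A, from 5% to 50%.

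Adjusting for A multiplies the residual SD by sqrt(1 - f). The effective standardised effect is d / sqrt(1 - f), and the noncentrality parameter of the two-sample t test is [d / sqrt(1 - f)] x sqrt(50/2). For d = 0.5 and f = 0 this is 0.5 x 5 = 2.5. For f = 0.2 it is 0.559 x 5 = 2.795.

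| f | effective effect (d = 0.5) | power, d = 0.5 |
|---|---|---|
| 0 (unadjusted) | 0.500 | 69.7% |
| 5% | 0.513 | 71.9% |
| 10% | 0.527 | 74.2% |
| 20% | 0.559 | 79.0% |
| 50% | 0.707 | 93.8% |

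At d = 0.8, power is 97.7% unadjusted and 99.3% with f = 20%, so there is almost nothing to gain.

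**The case against.** **The text may be loose rather than contradictory.** The CNP description can be read as work-up that continues after the infarction is recognised and the patient allocated. A diagnosis made before allocation does not rule out further diagnostic steps after it. A condensed article may also leave the moment of consent and envelope opening to the full protocol. This stands in part: silence on timing is not itself the finding. What remains is that the printed eligibility rule, the first CNP component and an outcome timed from the door do not fit together without a further statement.

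**The control-arm wording is weak evidence.** Care before hospitalisation refers to admission, which is neither the hospital door nor randomisation. The control electrocardiogram can be read as monitoring. This stands, and the point does not rely on either.

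**A stronger reading is tempting.** A reader might infer that envelopes are opened at the door, that patients who turn out not to have ST-elevation infarction are randomised, and that staff who know the arm then remove them, which would break the comparison. A reader might also infer that CNP diagnosis is given before allocation, so that the arm is in effect chosen beforehand. The article says neither. It enrols patients already diagnosed, which points to allocation after diagnosis.

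**The harm is modest and its size is assumed.** This stands. On the supported reading the comparison is unbiased, and the other four outcomes are largely unaffected. The gain from adjustment is small if pre-randomisation time explains little of the variance or if the effect is as large as the Discussion hopes.

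**Conclusion.** The mismatch is real but limited. On the reading the text best supports, the first diagnosis is not part of what is randomised, and door-to-randomisation time adds variance without bias. The door-to-balloon comparison is therefore valid but less precise than it could be, and it cannot support a claim that CNP speeds diagnosis.

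The loss of precision cannot be determined from the article. In the illustration, adjustment raises power from 70% to between 72% and 94%, assuming a 0.5 SD effect and a variance share of 5% to 50%. The gain is negligible at 0.8 SD. The conclusion about interpretation depends on none of these figures, only on allocation following diagnosis and on equal care in both arms until then. The documents do not support a conclusion that the comparison is biased by exclusions after randomisation.

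**What to change.** - Reconcile 2.2 and 2.3: state that the envelope is opened only after eligibility is confirmed, and list which CNP components start at that moment.
- Record the time of opening.
- Keep door-to-balloon time as the outcome, but analyse it with door-to-randomisation minutes as a covariate. Under this rule the covariate is fixed before allocation, so adjusting for it is safe.
- Report randomisation-to-balloon time beside it, as the interval that the assigned care can change.
- State that speed of the first diagnosis is not part of the randomised comparison.

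The cost is one extra time stamp on the case form and a few sentences. The real price is a narrower claim: the trial could not say that CNP speeds diagnosis. If the sponsor wants to test that component, individual allocation after diagnosis cannot do it. A different design would be needed, for example allocation by period or by team.

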### Outcomes

2.4

Among the 2 groups, the time from door to balloon, hospitalization expenses, length of stay, postoperative complications, patient's satisfaction with treatment are compared and analyzed.

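### Door-to-balloon time and postoperative complications both depend on reaching PCI, an event after randomisation that the nursing pathway can itself influence

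*Protocol article*

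**What the plan says.** All references are to the protocol article.

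- **Eligibility (2.2 Subjects).** Patients have ST-elevation infarction and "emergency transradial PCI therapy is necessary". A completed PCI is not required.
- **Size (2.2 Subjects).** "Hundred patients with diagnosed acute myocardial infarction (AMI) will be included in this experiment", with "control group, accepting normal nursing plan, containing 50 patients". The size of the pathway arm is not given; by subtraction it is 100 − 50 = 50.
- **Intervention (2.3 Nursing protocol).** In the pathway arm, care begins at the front end: "The patients is dealt with rapid diagnosis, then there is a more precise examination". Vital-sign support, emergency drugs and fast transfer to specialists follow. The description then continues through the stay to discharge.
- **Outcomes (2.4).** "the time from door to balloon, hospitalization expenses, length of stay, postoperative complications, patient's satisfaction with treatment are compared and analyzed". Death, events before the procedure and PCI not performed are not listed.
- **Analysis (2.5).** "Continuous variables are showed as mean (standard deviation) and analyzed by paired *t* tests or independent *t* tests". Categorical outcomes are given as percentages of patients; which patients form the denominator is not said.
- **Hypothesis (4 Discussion).** The authors expect improvement on all five outcomes.

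**The concern.** Randomisation makes the arms comparable at entry. A comparison restricted to patients who later reach some point in care keeps that protection only if the treatment does not affect who reaches it. Here the point is PCI, and the pathway includes care given on the way to it.

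Two outcomes are tied to that point. Door-to-balloon time has no value without a balloon. The complication count, by its wording, opens after the operation. A patient who arrests or dies while waiting, who turns out at angiography to need no balloon, or who is diverted to surgery has no door-to-balloon time. An arrest before the procedure is not a postoperative complication in either arm, and no other listed outcome records it.

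The bias can run either way. If the pathway brings more unstable patients to the table, their long times and later complications count against it, while similar control patients contribute neither. If instead it prevents events before the procedure, that benefit is not recorded. Published means and percentages would not show which had happened.

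**Working it through.** The article gives no effect size, SD, event rate or non-arrival rate, so there is no figure to reproduce. The calculations below show scale only.

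**Step 1: does the dependence follow from the text?** Eligibility needs PCI to be indicated, not done (2.2). The moment of randomisation is not stated, but the pathway covers diagnosis and transfer (2.3), so assignment must come before PCI if the pathway is to be delivered as described. One outcome needs a balloon and another starts after the operation (2.4). A comparison of means has no entry for a patient without a time (2.5). Reaching PCI is therefore an event after randomisation on which two of the five outcomes depend.

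**Step 2: door-to-balloon time, worst case.** Assumptions: 50 per arm; log-normal times with median 80 min and log-SD 0.4 in both arms; no true effect; one arm alone loses its slowest k patients, with k from 1 to 5 (2% to 10%).

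- Mean = 80 × exp(0.4²/2) = 86.7 min.
- SD = 86.7 × √(exp(0.4²) − 1) = 36.1 min.
- SE of the difference = 36.1 × √(2/50) = 7.2 min.

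By simulation, with the shift divided by 7.2 for the third column:

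| Lost from one arm | Fall in that arm's mean | In SE of the difference | Two-sided false-positive rate of the t test |
|---|---|---|---|
| 1 | 2.3 min | 0.32 | 7% |
| 2 | 4.1 min | 0.57 | 10% |
| 3 | 5.6 min | 0.78 | 14% |
| 5 | 8.3 min | 1.15 | 25% |

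With normal instead of log-normal times, a truncated-normal calculation for losing the slowest 2%, 4%, 6% or 10% gives shifts of 0.05, 0.09, 0.13 or 0.20 SD and rejection rates of about 6%, 7.5%, 10% or 18%.

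**Step 3: equal loss.** With 50 per arm and two-sided 0.05, the difference detectable at 80% power is (1.960 + 0.842) × √(2/50) = 0.56 SD. If 2%, 5% or 10% of both arms have no time, for reasons unrelated to how long they would have waited, power falls to 79%, 78% or 76%. Loss of numbers is minor; unequal, selective loss is what matters.

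**Step 4: complications.** One uncounted event is 1/50 = 2 percentage points, provided the patient stays in the denominator as complication-free (for example 10/50 = 20% instead of 11/50 = 22%). If the patient also leaves the denominator, the rate is 10/49 = 20.4%, a gap of 1.6 points. With an assumed 10 counted events, removing 1, 3 or 5 patients from the denominator alone moves 20.0% to 20.4%, 21.3% or 22.2%. The missing event matters more than the shrinking denominator.

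**The case against.** **This may be settled in the full protocol or SAP.** In part, yes. The analysis population, the scoring of a missing time and the complication denominator are details that a condensed article often leaves out. A reader might infer that patients without a balloon are dropped from both outcomes, or that the complication denominator is wrong. The article says neither: only the absence of a door-to-balloon time is certain, and a patient without PCI may remain in the complication denominator. What an SAP would not normally change is the outcome definition, and Section 2.4 fixes the count as postoperative.

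**Pathway care is not only pre-procedure.** This stands. A reader might take the statement that the nursing group "uses emergency equipment and appropriate drugs to prevent adverse events" as care before PCI, but its position in Section 2.3, after the admission plan and just before the discharge sentence, does not fix its timing. Nor are these two the only outcomes the pathway is meant to change; the Discussion names all five. The point needs only that some pathway care precedes PCI, and the opening steps of Section 2.3 do.

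**Postoperative complications suit the stated aim.** The article asks about the clinical efficacy of transradial emergency PCI, and a count from randomisation is less specific to PCI. That is a fair cost, and a reason to keep the postoperative count as a subset.

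**The numbers are a worst case.** Also true. Losses confined to one arm and to its slowest patients are an extreme. One or two lost patients shift the difference by only 0.3 to 0.6 SE. Requiring that PCI be necessary, obtaining signed consent and excluding organ damage may all keep non-arrival low.

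**Conclusion.** The concern holds in a limited form. Two of the five outcomes are conditional on reaching PCI, the pathway acts partly before PCI, and no listed outcome captures death or failure to reach it. If non-arrival or pre-procedure events differ between arms, these two comparisons are biased, with the direction unknown.

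The size cannot be known from the documents. The shift of about 2 to 8 min in one arm's mean rests on an assumed loss of 1 to 5 of 50, all from one arm and all its slowest, and on the assumed log-normal distribution. It is an upper illustration, not a forecast. The 2 percentage points per uncounted event is plain arithmetic on a 50-patient arm. Similar loss in both arms, unrelated to delay, would cost little. The change is worth making because it is cheap and the bias would otherwise go unseen.

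**What to change.** 1. In Section 2.4, count death and complications from randomisation (before, during and after PCI), with all randomised patients in the denominator. Show postoperative events as a subset.
2. Report by arm how many randomised patients had no balloon, and why.
3. Keep the door-to-balloon comparison among patients who had a balloon. Add a sensitivity analysis over all randomised patients, with a score fixed in advance for every reason for having no balloon: death or deterioration, no balloon needed, diversion to surgery. Ranking only deaths and deteriorations as worst would leave the other reasons unscored. Making such a ranking the main analysis would also change both the estimand and the planned t test, so it belongs in the sensitivity analysis.

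**Cost.** Edits to Sections 2.4 and 2.5, collection of events and reasons from randomisation onward, and one extra analysis; no additional patients. The downside is that the overall complication rate will include events of the infarction itself and so be less specific to PCI; the postoperative subset keeps that information.
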